### 4. Required equipment and supplies

The drugs to be used in the study will be supplied by the Cambodian Ministry of Health. The required equipment for the molecular marker assays, including the PCR, RT-PCR and Luminex instruments are available at the NAMRU-2/NIPH lab in Phnom Penh, at the Institute Pasteur de Cambodge, and, at the National Malaria Center in Phnom Penh. The reagents required for the assays, probes, primers, PCR and RT-PCR reagents are perishable. Quantities adequate to begin the study are on hand or already ordered as of May 2009. Additional perishable supplies will be purchased as required.

### 5. Budget

|  |  | Year 1 | Year 2 | Total |
| --- | --- | --- | --- | --- |
| Travel |  | 6000 | 6000 | 12000 |
| Reagents |  |  |  |  |
|  | Assay DHFR SNPs | 7000 | 7000 | 14000 |
|  | Assay DHPS SNPs | 4950 | 4950 | 9900 |
|  | Assay Pfcrt SNP | 1900 | 1900 | 3800 |
|  | Assay Pfmdr Copy # | 3680 | 3680 | 7360 |
|  | Assay Pfmdr SNPs | 5500 | 5500 | 11000 |
| Consumables |  | 6000 | 6000 | 12000 |
| Communication |  | 2000 | 2000 | 4000 |
| Locally Hired Staff/Contracts |  | 27600 | 28000 | 55600 |
| Total |  | 64630 | 65030 | 129660 |

### 2. Multicenter Organizational Plan for IRB Review and Approval

The protocol will undergo scientific review by the NAMRU-2 Scientific Review Board. Ethical review will be performed by the National Ethics Committee of Cambodia and the NAMRU-2 IRB. The Naval Medical Research Center Office of Research Administration and Bureau of Medicine each provide subsequent quality assurance review, but the study may begin once final approvals by the National Ethics Committee of Cambodia and NAMRU-2 have been granted. Continuing review of the study for NAMRU-2 will be conducted by the IRB of the Naval Medical Research Center, Silver Spring Maryland, pending re-establishment of the NAMRU-2 IRB in Phnom Penh.

### 3. Technology Transfer/Capacity Building/Sample Sharing Plan

The conduct of this protocol will strengthen the capacity of Cambodian scientists at all participating institutions to perform assays to detect molecular markers of drug resistance, including real-time PCR and Luminex flow-cytometry based assays. The use of these assays will, ultimately facilitate monitoring the spread of drug resistant strains of *P. falciparum*. All molecular assays will be performed in Cambodia at one of the collaborating institutions. Samples will be shared freely between the collaborating institutions in Cambodia in order to complete the assays included in this study. It is not anticipated that any biosamples will be sent out of Cambodia in the course of this protocol.

## D. RISKS AND BENEFITS FOR SUBJECTS

### 1. Risks

There are three main risks in the study, the risk of treatment failure due to drug resistance, the risk of known side effects of the three standard anti-malarial regimens used, and risks associated with venipuncture and fingerprick blood sampling.

Treatment failure

There is a small, but very real risk of treatment failure with all three of the standard treatment regimens. There has been recent evidence of diminished efficacy of mefloquine-artesunate in some areas of Cambodia (10), but no such evidence from Oddarmeanchey Province. Recent WHO studies in Western Cambodia found efficacies for both Malarone and piperaquine-DHP of >95%.

#### Side effects of standard anti-malarial drugs

The three treatment regimens to be evaluated are either included in current Cambodian Ministry of Health guidelines for treatment of uncomplicated *P. falciparum* malaria (mefloquine-artesunate and piperaquine-DHA) or are recommended for use in drug resistance containment programs in Cambodia by the World Health Organization (Malarone). Their safety profiles are well understood and their adverse effects are mild compared to the risks of untreated *P. falciparum* malaria. Similarly, the adverse event profile of the rescue therapy, quinine-tetracycline, is well understood. Side effects of anti-malarials used for treatment of acute malaria, rather than for prophylaxis, may be difficult to distinguish from the symptoms of malaria. Possible side effects of the treatment regimens are as follows:

*Mefloquine-artesunate*

Side effects occurring in more than 1% of treated subjects may include dizziness, myalgias, fever, vomiting, headache, chills diarrhea, skin rash, abdominal pain, fatigue, loss of appetite, and tinnitus.

*Piperaquine-DHA*

Side effects occurring in more than 1% of treated subjects may include nausea, vomiting, and anorexia.

*Malarone (atovaquone-proguanil)*

Side effects occurring in more than 1% of treated subjects may include abdominal pain, nausea, vomiting, headache, diarrhea, weakness, loss of appetite and dizziness.

Quinine-doxycycline

Side effects occurring in more than 1% of treated subjects include headache, tinnitus, nausea, vomiting, blurred vision, and vertigo. Cardiac side effects from quinine are a significant risk for intravenous administration, but are very rare following oral administration.

#### Side effects of blood sampling

Venipuncture and finger prick blood sampling carry a risk of mild discomfort and a very small risk of infection. The risk of infection will be minimized by the use of aseptic technique and disposable, sterile needles and lancets.

#### Social or economic risks

Neither malaria infection nor anemia is associated with any social stigma, and there is no local health insurance scheme which could use information about anemia or malaria infection to the disadvantage of any subject. There therefore do not appear to be significant social or economic risks to participating in the study.

### 2. Benefits

Participants in the study will receive one of three standard anti-malarial therapies which make up part of Cambodia’s malaria control program. In addition, they will receive more extensive post-treatment monitoring to detect treatment failure than they would routinely. They will receive prompt rescue therapy in the event of treatment failure. In addition they may receive some satisfaction from contributing to efforts to control malaria in Cambodia.

### 3. Confidentiality and Sample Storage

Case report forms will be stored in locked file cabinets at the field sites and then transported to the National Center for Malaria, where they will be stored in a locked office and will only be accessed by members of the study team or officials with responsibility for study oversight.

Samples collected as part of this study will be maintained in locked drawers or freezers in the National Malaria Center, the Pasteur Institute, or the NAMRU-2/NIPH laboratory. Samples will be used only for the purposes of the study described in this protocol and any excess will be destroyed upon completion of the study.

### 4. Special Risks to Pregnant or Potentially Pregnant Women Volunteers

Female subjects over age 12 must have a negative urine pregnancy test before enrolling in the study. Pregnant patients will not be enrolled in the study.

### 5. Safety Precautions and Emergency Procedures

The risk of morbidity or mortality resulting from treatment failure will be greatly reduced by the careful monitoring for early detection and treatment of recurrent parasitemia. The side effects of treatment with all of the standard anti-malarial regimens used in this study are well understood. Individuals who have contraindications for or known hypersensitivity to any of the anti-malarials in the study will be excluded from the study. The anti-malarials are well tolerated and the risks are reasonable in treatment of a potentially fatal disease. Risks associated with venipuncture and finger prick blood sampling will be minimized as described above.

### 6. Assessment of Sufficiency of Plans to Deal with Untoward Events or Injuries

This study will be conducted at government health center in a rural area in Cambodia. The research team will keep one physician on site 24 hours a day, 7 days a week for the duration of the study. The supervising physician will always maintain a field medical bag available for emergency care of study subjects. In the event of medical emergencies unrelated to study participation, the study team will facilitate access to the healthcare system to the extent practical.

### 7. Qualification of Medical Monitor and Medical Support Personnel

The Medical Monitor, [name], is a senior physician at the National Malaria Center with over 20 years experience treating patients with malaria. [name], the principal investigator, is a physician at the National Malaria Center, with extensive experience in malaria treatment.

## E. DESCRIPTION OF THE SYSTEM FOR MAINTENANCE OF RECORDS

### 1. Experimental Data

Experimental data will be maintained in the form of case report forms stored in a locked file cabinet in a locked room in the National Malaria Center; laboratory results will be stored on password protected computers at the National Malaria Center, the Institute Pasteur de Cambodge, and the NAMRU-2/NIPH laboratory.

### 2. Regulatory File

The original research protocol, consent forms, and related documents for protection of human research volunteers will be stored at the National Malaria Center with copies stored NAMRU-2/NIPH. At both institutions these documents will be stored in locked cabinets in locked offices.

### 3. Individual Medical Records

Clinical and laboratory findings from each subject will be kept in individual folders of CRF. These CRFs contains the subject’s name and study code number. This represents the only link established between the subject and the study code number. During the study, the CRFs are held in a secured cabinet with access restricted to research team members with a need to use the CRF. Team members with access to CRFs are counseled on the importance of confidentiality of subject medical records. All NAMRU-2 staff involved in this study have completed Navy Office of Research Administration-sponsored ethics training and hold an IRB certification number. In all electronic records for data analysis, the subject is not referenced by name, but only study code number. This method is designed to protect the privacy of study subject medical information. All CRFs will be held at CNM for at least 5 years in secured cabinets with restricted access.

A report summarizing the findings of this trial will be forwarded to all collaborating institutions (via the co-investigators on this protocol). A record of this research published in a peer-reviewed journal is anticipated.

# Figure 1. Malaria Containment Zones.

[figure not shown]

# Appendix A. Case Report Form

1

| Subject number: FTP __ __ __ | Visit Date:  ___ ___/ ___ ___ ___/2009  DD MMM YYYY | **Pre-treatment** |
| --- | --- | --- |

| **SENTINEL SITE** | | | |
| --- | --- | --- | --- |
| Name of the health center: | Locality: | | District: |
| Address: | | Province: | |

| **DEMOGRAPHIC DATA** |
| --- |
| Age: ___ ___ years Gender (please tick  only one box):  Male  Female  Weight: ___ ___ ___ . ___ kg |
|  |

| **PRE-TREATMENT TEMPERATURE** |
| --- |
| Axillary Temperature: ___ ___ . ___ °C  History of fever within previous 24 hours  Yes  No |

| **THICK AND THIN BLOOD SMEARS** |
| --- |
| Which species? *P. falciparum*  *P. vivax**  *P. ovale**  *P. malariae**  Mixed species*  ***NOT ELIGIBLE** |

| **PARASITE DENSITY** |
| --- |
| For *P. falciparum* ***o*nly** (I,000-100,000/µL): >40/200 WBC AND <25/1000 RBC  Yes  No*  ***NOT ELIGIBLE** |

| **URINE PREGNANCY TEST** (This section applies only to female patients.) |
| --- |
| Result of pregnancy test:  Negative  Positive* **(NOT ELIGIBLE)** |

| **INCLUSION CRITERIA** |
| --- |
| 1. Male or female patients ≥5 year of age 2. Presence of acute symptomatic uncomplicated *P. falciparum* malaria with a diagnosis confirmed by a positive blood smear with *P. falciparum* only (i.e. no mixed infection)    - acceptable range is between 1,000 and 100,000 asexual parasites/µl of blood 3. Measured axillary temperature of ≥37.5°C, tympanic temperature ≥38.0oC or history of fever within previous 24 hours 4. Ability to swallow oral medication 5. Negative urine pregnancy test (if female ≥12 years of age) 6. Willingness and ability to comply with study protocol and with study visit schedule for the duration of the study 7. Willingness to give informed consent |
| Does the patient meet all of the inclusion criteria?  Yes  No |

| **EXCLUSION CRITERIA** |
| --- |
| 1. Age < 5 years  2. Mixed species infection (e.g. *P. falciparum* and *P. vivax*)  3. Positive urine pregnancy test or lactating  4. History of epilepsy or psychiatric illness  5. Any of the following WHO criteria for severe malaria  Clinical malaria with any one or more of the following clinical manifestations:  i) Unrousable coma or Blantyre Coma Score of 3 or less; coma persists for more than 30 minutes after fits have ceased.  ii) Generalised convulsions lasting more than 30 minutes or more than 2 fits in 24 hours despite cooling  iii) Haemoglobin < 5g/dL  iv) Presence of any of the following; alar flaring, chest recession (intercostals or sub costal), use of accessory muscles of respiration; abnormally deep (acidotic) breathing.  v) Hypoglycaemia (blood glucose < 2.2mM/L[<40 mg/dL])  vi) Circulatory collapse (systolic bp <50mm Hg)  vii) Renal failure (urine output less than 12ml/kg/24hrs; or serum creatinine conc >3.0mg/dL)  viii) Malarial haemoglobinuria  ix) hyperparasitaemia (>100,000 /µl)  x) Jaundice (serum bilirubin ≥ 3.0mg/dL),  xi) Impaired consciousness (but rousable) OR  General danger signs of severe illness in children   - Inability to drink or breastfeed - Repeated vomiting - Recent history of convulsions - Lethargy or unconsciousness - Inability to sit or stand up   6. Serious co-morbid conditions requiring hospitalization (including, but not limited to severe renal or liver disease, uncontrolled diabetes, systemic bacterial infections).  7. On-going antibiotic therapy  8. Known history of hypersensitivity, allergic or adverse reactions to the drugs used in this study  9. Plans to leave area during next 42 days or to be unavailable for scheduled follow-up  10. Nursing mother  11. Any other condition which, in the judgment of the study physician would make participation in the study unsafe for the potential volunteer. |
| Does the patient meet any of the exclusion criteria?  Yes  No |
| If yes, please specify reason of exclusion: |

| **PATIENT INFORMED CONSENT AND ASSENT** | | |
| --- | --- | --- |
| Consent Form signed:  Yes  No  Assent Form signed:  Yes  No | Date: ___ ___/ ___ ___ ___/2009 | Subject Number:  FTP __ __ __ |

| Subject number: FTP __ __ __ | **Treatment**  **(Day 0)** |
| --- | --- |

| **DEMOGRAPHIC DATA** |
| --- |
| Occupation: ____________________________________________________  Possible place of Infection (where did you go in the last 2 weeks?): _______________________________________________ |
| How many days have you been sick? **___ ___** days  History of drug allergy:  No  Yes, what drug? __________________________________________________ |

| **HEMATOCRIT** |
| --- |
| Hematocrit ___ ___ % |

| **BLOOD SMEARS FOR QUANTITATIVE PARASITE COUNTS AND QUALITATIVE GAMETOCYTE COUNTS** | | | |
| --- | --- | --- | --- |
| ***P. falciparum*** | | | |
| Was species other than *P. falciparum* detected upon review of slides?  If yes, the patient is to be excluded. | Number of asexual *P. falciparum* parasites | | Presence of *P. falciparum* gametocytes?   No  Yes, rare   Yes, easy to find |
| /200 WBC | /1,000 RBC  (if>100/HPF on thick) |
|  Yes  No | ­­­­­­­­­­­­­­­­­___ ___ ___ ___ | ___ ___ ___ |

| **PRIOR MEDICATION** | | | | | |
| --- | --- | --- | --- | --- | --- |
| Has the patient taken any prior antimalarial medication?  Yes  No  If yes, please specify on this page. | | | | | |
| * All prior medication, including natural remedies and homeopathic drugs, taken within the previous 14 days should be reported in this section. Either Stop date or Ongoing should be filled in. | | | | | |
| Drug name  *(Generic name)* | Start date/Stop date  (DD/MMM/YYY) | Ongoing  ( if Yes) | Total daily  Dose & unit | Route of administration | Indication for use |
|  | ___ ___/___ ___ ___/2006  ___ ___/___ ___ ___/2006 |  |  |  |  |
|  | ___ ___/___ ___ ___/2006  ___ ___/___ ___ ___/2006 |  |  |  |  |

| Subject number:  FTP __ __ __ | Visit Date:  ___ ___/ ___ ___ ___/___ ___ | **Treatment**  **(Day 0)** |
| --- | --- | --- |

| **Physical Examination** |
| --- |
| Time:  ___ ___ : ___ ___ (HH:MM) |
| **Vital Signs** |
| Time of measurement: ___ ___ : ___ ___ (HH:MM) |
| Systolic blood pressure (SBP)/Diastolic blood pressure (DBP): ___ ___ ___ / ___ ___ ___ |
| Heart Rate: ___ ___ ___ b.p.m. |
| Axillary Temperature: ___ ___ . ___ °C |

|  | Please tick  the applicable box | | |  |
| --- | --- | --- | --- | --- |
| **Body System** | **Normal** | **Abnormal** | **Not examined** | **Findings (if abnormal)** |
| General Appearance |  |  |  |  |
| Head and Eyes |  |  |  |  |
| Ears, Nose and Throat |  |  |  |  |
| Chest and Lungs |  |  |  |  |
| Cardiovascular |  |  |  |  |
| Abdomen |  |  |  |  |
| Neurological |  |  |  |  |
| Lymphatic (excluding head and neck) |  |  |  |  |
| Musculo-skeleton |  |  |  |  |
| Other, specify: |  |  |  |  |
| Other, specify: |  |  |  |  |
| Other, specify |  |  |  |  |
| **Subject number:** FTP ______ | | | | |

| **Assessment of Clinical signs and Symptoms** | | | |
| --- | --- | --- | --- |
| **Signs and Symptoms** | **Present** | **Absent** | **Note** |
| Rigors/Chills |  |  |  |
| Sweating |  |  |  |
| Headache |  |  |  |
| Cough |  |  |  |
| Nausea |  |  |  |
| Vomiting |  |  |  |
| Loss of appetite |  |  |  |
| Fatigue |  |  |  |
| Myalgia |  |  |  |
| Jaundice |  |  |  |
| Hepatomegaly |  |  |  |
| Splenomegaly |  |  |  |
| Other (1) |  |  |  |
| Other (2) |  |  |  |

| The Examining Physician:  Name Signature |
| --- |

| **STUDY MEDICATION ADMINISTRATION** | | | | |
| --- | --- | --- | --- | --- |
| Name of the **antimalarial** drugs | Time of dosing  (HH:MM) | Number of  tablets | Did the patient  vomit? | Time of vomiting  (HH:MM) |
|  | ___ ___:___ ___ | ___ ___ |  Yes  No | ___ ___:___ ___ |
|  | ___ ___:___ ___ | ___ ___ |  Yes  No | ___ ___:___ ___ |
|  | ___ ___:___ ___ | ___ ___ |  Yes  No | ___ ___:___ ___ |

| **ADJUNCTIVE MEDICATIONS** | | | | |
| --- | --- | --- | --- | --- |
| Name of other medicines | Time of dosing  (HH:MM) | Number of tablets | Did the patient  vomit? | Time of vomiting  (HH:MM) |
|  | ___ ___:___ ___ | ___ ___ |  Yes  No | ___ ___:___ ___ |
|  | ___ ___:___ ___ | ___ ___ |  Yes  No | ___ ___:___ ___ |

| Subject number: FTP __ __ __ | Date:  ___ ___/ ___ ___ ___/2006  DD MMM YYYY | **Treatment**  **(Day 1)** |
| --- | --- | --- |

| **CLINICAL STATUS** |
| --- |
| Presence of signs of severe or complicated malaria?  Yes  No |

| **TEMPERATURE** |
| --- |
| Axillary Temperature: ___ ___ . ___ °C |

| **BLOOD SMEARS FOR QUANTITATIVE PARASITE COUNTS AND QUALITATIVE GAMETOCYTE COUNTS** | | | |
| --- | --- | --- | --- |
| ***P. falciparum*** | | | |
| Is species other than *P. falciparum* present? | Number of  *P. falciparum* parasites (/200 WBC) | | Presence of  *P. falciparum* gametocytes? |
|  Yes  No | ___ ___ ___ ___ | |  Yes  No |
| **ADVERSE EVENTS** | | | |
| Presence of an adverse event?  Yes  No | | Is it a serious adverse event?  Yes  No  If yes, contact [name] ([contact]) within 24 hours | |
| Nature of the adverse event: | | | |

| **STUDY MEDICATION ADMINISTRATION** | | | | |
| --- | --- | --- | --- | --- |
| Name of the **antimalarial** drugs | Time of dosing  (HH:MM) | Number of  tablets | Did the patient  vomit? | Time of vomiting  (HH:MM) |
|  | ___ ___:___ ___ | ___ ___ |  Yes  No | ___ ___:___ ___ |
|  | ___ ___:___ ___ | ___ ___ |  Yes  No | ___ ___:___ ___ |
|  | ___ ___:___ ___ | ___ ___ |  Yes  No | ___ ___:___ ___ |

| **ADJUNCTIVE MEDICATION** | | | | |
| --- | --- | --- | --- | --- |
| Name of other medicines | Time of dosing  (HH:MM) | Number of tablets | Did the patient  vomit? | Time of vomiting  (HH:MM) |
|  | ___ ___:___ ___ | ___ ___ |  Yes  No | ___ ___:___ ___ |
|  | ___ ___:___ ___ | ___ ___ |  Yes  No | ___ ___:___ ___ |

| Subject number: FTP __ __ __ | Date:  ___ ___/ ___ ___ ___/2009  DD MMM YYYY | **Treatment**  **(Day 2)** |
| --- | --- | --- |

| **CLINICAL STATUS** |
| --- |
| Presence of signs of severe or complicated malaria?  Yes  No |

| **TEMPERATURE** |
| --- |
| Axillary Temperature: ___ ___ . ___ °C |

| **BLOOD SMEARS FOR QUANTITATIVE PARASITE COUNTS AND QUALITATIVE GAMETOCYTE COUNTS** | | | |
| --- | --- | --- | --- |
| ***P. falciparum*** | | | |
| Is species other than *P. falciparum* present? | Number of  *P. falciparum* parasites (/200 WBC) | | Presence of  *P. falciparum* gametocytes? |
|  Yes  No | ___ ___ ___ ___ | |  Yes  No |
| **ADVERSE EVENTS** | | | |
| Presence of an adverse event?  Yes  No | | Is it a serious adverse event?  Yes  No  If yes, contact [name] ([contact]) within 24 hours | |
| Nature of the adverse event: | | | |

| **STUDY MEDICATION ADMINISTRATION** | | | | |
| --- | --- | --- | --- | --- |
| Name of the **antimalarial** drugs | Time of dosing  (HH:MM) | Number of  tablets | Did the patient  vomit? | Time of vomiting  (HH:MM) |
|  | ___ ___:___ ___ | ___ ___ |  Yes  No | ___ ___:___ ___ |
|  | ___ ___:___ ___ | ___ ___ |  Yes  No | ___ ___:___ ___ |
|  | ___ ___:___ ___ | ___ ___ |  Yes  No | ___ ___:___ ___ |

| **ADJUNCTIVE MEDICATION** | | | | |
| --- | --- | --- | --- | --- |
| Name of other medicines | Time of dosing  (HH:MM) | Number of tablets | Did the patient  vomit? | Time of vomiting  (HH:MM) |
|  | ___ ___:___ ___ | ___ ___ |  Yes  No | ___ ___:___ ___ |
|  | ___ ___:___ ___ | ___ ___ |  Yes  No | ___ ___:___ ___ |

| Subject number: FTP __ __ __ | Date:  ___ ___/ ___ ___ ___/2009  DD MMM YYYY | **Treatment**  **(Day 3)** |
| --- | --- | --- |

| **CLINICAL STATUS** |
| --- |
| Presence of signs of severe or complicated malaria?  Yes  No |

| **TEMPERATURE** |
| --- |
| Axillary Temperature: ___ ___ . ___ °C |

| **BLOOD SMEARS FOR QUANTITATIVE PARASITE COUNTS AND QUALITATIVE GAMETOCYTE COUNTS** | | | |
| --- | --- | --- | --- |
| ***P. falciparum*** | | | |
| Is species other than *P. falciparum* present? | Number of  *P. falciparum* parasites (/200 WBC) | | Presence of  *P. falciparum* gametocytes? |
|  Yes  No | ___ ___ ___ ___ | |  Yes  No |
| **ADVERSE EVENTS** | | | |
| Presence of an adverse event?  Yes  No | | Is it a serious adverse event?  Yes  No  If yes, contact [name] ([contact]) within 24 hours | |
| Nature of the adverse event: | | | |

| **STUDY MEDICATION ADMINISTRATION** | | | | |
| --- | --- | --- | --- | --- |
| Name of the **antimalarial** drugs | Time of dosing  (HH:MM) | Number of  tablets | Did the patient  vomit? | Time of vomiting  (HH:MM) |
|  | ___ ___:___ ___ | ___ ___ |  Yes  No | ___ ___:___ ___ |
|  | ___ ___:___ ___ | ___ ___ |  Yes  No | ___ ___:___ ___ |
|  | ___ ___:___ ___ | ___ ___ |  Yes  No | ___ ___:___ ___ |

| **ADJUNCTIVE MEDICATION** | | | | |
| --- | --- | --- | --- | --- |
| Name of other medicines | Time of dosing  (HH:MM) | Number of tablets | Did the patient  vomit? | Time of vomiting  (HH:MM) |
|  | ___ ___:___ ___ | ___ ___ |  Yes  No | ___ ___:___ ___ |
|  | ___ ___:___ ___ | ___ ___ |  Yes  No | ___ ___:___ ___ |

| Subject number: FTP __ __ __ | Date:  ___ ___/ ___ ___ ___/2009  DD MMM YYYY | **Treatment**  **(Day 7)** |
| --- | --- | --- |

| **CLINICAL STATUS** |
| --- |
| Presence of signs of severe or complicated malaria?  Yes  No |

| **TEMPERATURE** |
| --- |
| Axillary Temperature: ___ ___ . ___ °C |

| **BLOOD SMEARS FOR QUANTITATIVE PARASITE COUNTS AND QUALITATIVE GAMETOCYTE COUNTS** | | | |
| --- | --- | --- | --- |
| ***P. falciparum*** | | | |
| Is species other than *P. falciparum* present? | Number of  *P. falciparum* parasites (/200 WBC) | | Presence of  *P. falciparum* gametocytes? |
|  Yes  No | ___ ___ ___ ___ | |  Yes  No |
| **ADVERSE EVENTS** | | | |
| Presence of an adverse event?  Yes  No | | Is it a serious adverse event?  Yes  No  If yes, contact [name] ([contact]) within 24 hours | |
| Nature of the adverse event: | | | |

| **STUDY MEDICATION ADMINISTRATION** | | | | |
| --- | --- | --- | --- | --- |
| Name of the **antimalarial** drugs | Time of dosing  (HH:MM) | Number of  tablets | Did the patient  vomit? | Time of vomiting  (HH:MM) |
|  | ___ ___:___ ___ | ___ ___ |  Yes  No | ___ ___:___ ___ |
|  | ___ ___:___ ___ | ___ ___ |  Yes  No | ___ ___:___ ___ |
|  | ___ ___:___ ___ | ___ ___ |  Yes  No | ___ ___:___ ___ |

| **ADJUNCTIVE MEDICATION** | | | | |
| --- | --- | --- | --- | --- |
| Name of other medicines | Time of dosing  (HH:MM) | Number of tablets | Did the patient  vomit? | Time of vomiting  (HH:MM) |
|  | ___ ___:___ ___ | ___ ___ |  Yes  No | ___ ___:___ ___ |
|  | ___ ___:___ ___ | ___ ___ |  Yes  No | ___ ___:___ ___ |

| Subject number: FTP __ __ __ | Date:  ___ ___/ ___ ___ ___/2009  DD MMM YYYY | **Treatment**  **(Day __)**  14,21,28,35,X |
| --- | --- | --- |

| **CLINICAL STATUS** |
| --- |
| Presence of signs of severe or complicated malaria?  Yes  No |

| **TEMPERATURE** |
| --- |
| Axillary Temperature: ___ ___ . ___ °C |

| **BLOOD SMEARS FOR QUANTITATIVE PARASITE COUNTS AND QUALITATIVE GAMETOCYTE COUNTS** | | | |
| --- | --- | --- | --- |
| ***P. falciparum*** | | | |
| Is species other than *P. falciparum* present? | Number of  *P. falciparum* parasites (/200 WBC) | | Presence of  *P. falciparum* gametocytes? |
|  Yes  No | ___ ___ ___ ___ | |  Yes  No |
| **ADVERSE EVENTS** | | | |
| Presence of an adverse event?  Yes  No | | Is it a serious adverse event?  Yes  No  If yes, contact [name] ([contact]) within 24 hours | |
| Nature of the adverse event: | | | |

| **STUDY MEDICATION ADMINISTRATION** | | | | |
| --- | --- | --- | --- | --- |
| Name of the **antimalarial** drugs | Time of dosing  (HH:MM) | Number of  tablets | Did the patient  vomit? | Time of vomiting  (HH:MM) |
|  | ___ ___:___ ___ | ___ ___ |  Yes  No | ___ ___:___ ___ |
|  | ___ ___:___ ___ | ___ ___ |  Yes  No | ___ ___:___ ___ |
|  | ___ ___:___ ___ | ___ ___ |  Yes  No | ___ ___:___ ___ |

| **ADJUNCTIVE MEDICATION** | | | | |
| --- | --- | --- | --- | --- |
| Name of other medicines | Time of dosing  (HH:MM) | Number of tablets | Did the patient  vomit? | Time of vomiting  (HH:MM) |
|  | ___ ___:___ ___ | ___ ___ |  Yes  No | ___ ___:___ ___ |
|  | ___ ___:___ ___ | ___ ___ |  Yes  No | ___ ___:___ ___ |

| Subject number: FTP __ __ __ | Date:  ___ ___/ ___ ___ ___/2009  DD MMM YYYY | **Treatment**  **(Day 42**) |
| --- | --- | --- |

| **CLINICAL STATUS** |
| --- |
| Presence of signs of severe or complicated malaria?  Yes  No |

| **TEMPERATURE** |
| --- |
| Axillary Temperature: ___ ___ . ___ °C |

| **BLOOD SMEARS FOR QUANTITATIVE PARASITE COUNTS AND QUALITATIVE GAMETOCYTE COUNTS** | | |
| --- | --- | --- |
| ***P. falciparum*** | | |
| Is species other than *P. falciparum* present? | Number of  *P. falciparum* parasites (/200 WBC) | Presence of  *P. falciparum* gametocytes? |

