#### b. Study Location

The study will be conducted at the Trapeang Prasat Health Center in Oddarmeanchey Province, Cambodia. This site is in a rural, agricultural area about 8 hours by road from Phnom Penh. Falciparum malaria is common in the area around the health center. The health center participates in a current surveillance program to measure the prevalence of molecular markers of drug resistance in *P. falcparum*. In the first six months of surveillance, the health center enrolled 450 subjects over age 5. Of these, 433 (96%) had parasitemia > 1000 parasites/µl. The mean pfmdr1 copy number was 1.89 (95% CI 1.78, 2.00) and the proportion of samples with copy number >1.5 was 0.49. Although this prevalence of amplified *pfmdr1* genes is lower than at Chumkiri, the site at which we found an unexpectedly high failure rate for mefloquine-artesunate (10), it is elevated compared to sites in eastern Cambodia from which mefloquine resistance has not been reported. We expect, therefore, both that the number of eligible subjects will be sufficient and that there is a reasonable likelihood of finding mefloquine artesunate resistance in this site.

All laboratory analyses will be conducted at one of the collaborating Cambodian institutions, the National Malaria Center, or the Institute Pasteur de Cambodge. Confirmation of microscopic diagnosis of malaria will be performed at the National Malaria Center. RT-PCR based SNP and gene amplification assays for detection of molecular markers of drug resistance will be performed at Institute Pasteur or CNM; both these laboratories have experience in performing the RT-PCR assays. In vitro drug resistance assays will be performed at the Pasteur Institute.

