#### d. Inclusion and exclusion criteria

The inclusion criteria are as follows:

1) Age≥5 years

2) *P. falciparum* parasitemia >1000/µl blood, but <100,000/µl

3) Axillary temperature > 37.5oC or rectal or tympanic temperature > 38.0oC, or history of fever within past 24 hours.

4) Negative urine pregnancy test

5) Ability to swallow oral medication

6) Availability for follow-up over 42 days

7) Freely provides informed consent

Specific exclusion criteria are the following:

1) Age < 5 years

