#### f. Laboratory procedures

##### Malaria thick and thin blood films

Thick and thin blood smears will be stained with Giemsa and examined by a certified microscopist using 1000X oil immersion light microscopy. At least 200 ocular fields will be examined before a negative diagnosis is rendered. The microscopist records the number of asexual and sexual forms (separately) per 200 white blood cells in the thick smear. This is later converted to parasites/µl with a conversion multiple of 40 (assumes 8000WBC/µl) for analysis. All smears will be reviewed by a second certified microscopist at CNM. Slides for which results are discrepant will be reviewed by a third certified microscopist and the majority reading considered definitive. In the event that more than 10% of the reviewed slides show discrepancies, all study slides will be reviewed before data analysis.

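### The CRF parasite-density box tests for more than 1,600/µl under the protocol's own conversion, not the 1,000/µl in the inclusion criterion and the box's own label

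*Protocol*

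**What the plan says.** Section B.1.d of the Protocol admits *P. falciparum* "parasitemia >1000/µl blood, but <100,000/µl". The inclusion list on the pre-treatment page of the case report form (Appendix A, item 2) agrees: "acceptable range is between 1,000 and 100,000 asexual parasites/µl of blood". The density box on the same page carries that range in its label, but the test it sets is ">40/200 WBC AND <25/1000 RBC". A negative answer is flagged as making the patient not eligible.

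The section on malaria thick and thin blood films fixes the link between counts and densities. On counting, it says "The microscopist records the number of asexual and sexual forms (separately) per 200 white blood cells in the thick smear". On conversion, it says "This is later converted to parasites/µl with a conversion multiple of 40 (assumes 8000WBC/µl) for analysis". No other white-cell assumption appears in the document, and no red-cell count is stated anywhere.

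On site experience, section B.1.b reports 450 surveillance subjects over age 5 and adds: "Of these, 433 (96%) had parasitemia > 1000 parasites/µl".

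**The concern.** The box should restate the inclusion range in the units the microscopist counts in. Its lower limit does not. The figure 40 is the conversion multiple, and it stands where the count equivalent to 1,000/µl belongs. A patient with 30 parasites per 200 WBC (1,200/µl) fails the box and meets the density item in the list further down the same page.

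If staff follow the box, patients who meet the approved density criterion are refused, and they all come from the low-density end. If staff follow the criterion, the trial enrols subjects whose source record says they should not have been enrolled. The box matters because it is the one place in the document that states eligibility in raw counts, which is what the site has in hand at screening.

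**Working it through.** **Inputs from the Protocol**
- Lower density limit: 1,000/µl (B.1.d; form label; form inclusion item 2).
- Box threshold: more than 40 per 200 WBC (Appendix A).
- Conversion: multiply by 40, from 8,000 WBC/µl (blood films section).
- Site data: 433 of 450 above 1,000/µl (B.1.b).

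**The plan's own figure.** Density = count per 200 WBC × (WBC per µl ÷ 200). With 8,000 WBC/µl the multiple is 8,000 ÷ 200 = 40, as stated.

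**Lower limit**
- Box: 40 × 40 = 1,600/µl.
- Criterion: 1,000 ÷ 40 = 25 per 200 WBC.
- The box is 1,600 ÷ 1,000 = 1.6 times the criterion, or 60% too high.
- Whole-number counts above 1,000/µl that fail the box run from 26 (26 × 40 = 1,040/µl) to 40 (1,600/µl): 15 values.
- For 40 per 200 WBC to equal 1,000/µl, the white-cell count would have to be 1,000 × 200 ÷ 40 = 5,000/µl, which the Protocol does not state.

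**Upper limit.** 25 per 1,000 RBC is 2.5% of red cells. It equals 100,000/µl only at 4.0 million RBC/µl, which is an assumption. At 3.5 million it is 87,500/µl and at 5.0 million it is 125,000/µl.

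**Share of patients in the affected band (distribution assumed).** Take ln(density) as normal with SD σ, and fix the mean so that 17/450 = 3.8% lie at or below 1,000/µl. The matching normal quantile is −1.777, so mean = ln(1,000) + 1.777σ. With F the cumulative distribution, share = [F(1,600) − F(1,000)] ÷ [F(100,000) − F(1,000)].

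| σ | F(1,600) | F(100,000) | Share | Per 300 |
| --- | --- | --- | --- | --- |
| 1 | 0.0956 | 0.9977 | 0.0578 ÷ 0.9599 = 6.0% | 18 |
| 1.5 | 0.0716 | 0.9020 | 0.0339 ÷ 0.8642 = 3.9% | 12 |
| 2 | 0.0615 | 0.7004 | 0.0237 ÷ 0.6626 = 3.6% | 11 |

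**Possible effect on efficacy (illustration).** Suppose 5% of eligible patients were excluded, all of them would have been cured, and efficacy in the rest is 80%. The full-population figure would be 0.95 × 80 + 0.05 × 100 = 81%, a shift of 1 percentage point. The Protocol's own sample-size example puts the upper confidence limit at 87% for an observed 80% with 100 subjects, which is 7 points away.

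**A related mismatch.** The in vitro resistance assay section equates 40,000/µl with 160 per 200 WBC. With the multiple of 40, 160 per 200 WBC is 6,400/µl, and 40,000/µl is 1,000 per 200 WBC.

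**The case against.** The strongest reply is that the box need not govern. Section B.1.c tells the investigator to assess eligibility against the criteria in B.1.d, and the form gives the 1,000/µl limit twice. The conversion is also described as something done later, for analysis, so its use at screening is inferred. This stands against one tempting reading, that 1,600/µl is certainly the threshold the site applies. The documents show a form that contradicts itself, not which answer prevails. They do not remove the contradiction: the box's label and its test cannot both be right under the only conversion given.

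A reader might also infer that subjects enrolled with counts of 26 to 40 would be dropped from the per-protocol primary analysis. The data analysis section discusses that analysis only in terms of dropouts and losses to follow-up. It has no rule that removes anyone over an eligibility tick, so the inference is not supported.

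A reader might further conclude that the upper check is correct and only the lower figure is wrong. That rests on an unstated red-cell count, so the upper check is shown to be neither right nor wrong.

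Nor is recruitment threatened. The site enrolled 450 surveillance subjects in six months, and the trial needs 300 between August 2009 and October 2012. Patients found ineligible are referred for routine care.

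**Conclusion.** The lower limit in the box is inconsistent with section B.1.d, with the form's label and inclusion list, and with the stated conversion. That part is exact arithmetic on the Protocol's own figures. Patients counted at 26 to 40 per 200 WBC receive contradictory eligibility answers, and some may be wrongly excluded.

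The band's size is not documented. About 4 to 6% of otherwise eligible patients (11 to 18 per 300) is an estimate that depends on the log-normal shape, a log SD between 1 and 2, and the surveillance subjects resembling those screened for the trial. The effect on the efficacy estimates is probably small, and no primary conclusion is shown to change. The point is worth correcting because an eligibility threshold should have one meaning and the correction is nearly free.

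**What to change.** Change the lower limit in the box to more than 25 per 200 WBC, so that it matches the stated criterion and conversion. If 1,600/µl was the intended limit, leave the box and change section B.1.d, the box label and form inclusion item 2 instead.

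At the same time:
- write down the red-cell count that makes 25 per 1,000 RBC equivalent to 100,000/µl;
- reconcile the 160 per 200 WBC equivalence in the in vitro assay section with the multiple of 40.

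The cost is one number on one page of the form, one added assumption, and one reconciled figure. The design, the sample size and the analysis are unaffected.
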